## Methods and analysis

Here we describe a single arm, fixed sequence, single-blind, within-subjects study. Our primary outcomes investigate psychological flexibility through potential neurophysiological markers (specifically Lempel-Ziv complexity (LZc) recorded acutely using EEG, and the (Brief Experiential Avoidance Questionnaire (BEAQ) measured at baseline and primary endpoint). Secondary outcomes will provide a context to complement these mechanistic EEG data. Pain symptomatology will be measured using the Brief Pain Inventory Interference Subscale (BPI-IS) and broader aspects of health, including physical and mental health functioning will be measured using the 36-Item Short Form Health Survey (SF-36). We will additionally collect self-reported data on the strength of personally held negative beliefs in line with the relaxed beliefs under psychedelics model (55).

Further neurophysiological investigations will include functional magnetic resonance imaging (fMRI and DTI) (changes from baseline to primary endpoint), and EEG (changes from baseline to in putative resting state and ERP plasticity markers. We believe that a breakthrough on the brain mechanisms involved in therapeutically relevant change process catalysed by psilocybin, will have broad and important scientific and clinical implications.

Patient and public involvement (PPI) was used throughout the process of trial preparation and contributed to protocol development. PPI is an emerging research method across mental health and within psychedelic research (76, 77). The method aims to produce research “with” rather than “for” people with lived experience. Such co-created research fosters empowerment and trust in research produces relevant and transparent outputs (78).

PPI informed our therapeutic protocols, inspired further research questions, and resulted in the development of novel measures investigating the somatic elements of the psychedelic experience [see Bornemann et al. (79)]. Further, our panel of patient contributors has provided input to, and approved all patient facing documents.

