### Recruitment

We will recruit up to twenty participants with fibromyalgia as defined by the American Rheumatological Society 2016 diagnostic criteria (80). Study completion is set as completion of the final study visit (primary endpoint). Full entry criteria are outlined in **Table 1**.

**Table 1 T1:** Key In-/Exclusion criteria.

Inclusion criteria
Fibromyalgia Syndrome as diagnosed by an appropriate medical professional using the American College of Rheumatology diagnostic criteria, lasting for more than 3 months.
Over 18 years of age
UK resident registered with a primary care medical practice
Sufficiently competent in English with capacity to provide written informed consent
Agreement for research team to contact primary and/or secondary care team over the course of the study
No psychedelic use in the past 6 months

Exclusion criteria
Current or previously diagnosed psychotic disorder, bipolar disorder, or mania
Immediate family member with a diagnosed psychotic disorder
History of serious suicide attempts
Currently using medication which could interact with psilocybin including anti-psychotics, mood stabilizers & serotonergic antidepressants including SSRIs, SNRIs, and TCAs.*
Actively enrolled on pain management programme over course of study or awaiting further investigations for pain
On waiting list for interventional treatment for pain (e.g. surgery or targeted injections) Medical contraindications e.g., epilepsy, migraine, focal scalp sensitivity
MRI contraindications (e.g. metal implants)
Blood or needle phobia
People who are pregnant, planning to get pregnant, or currently breastfeeding
Unable to engage with physical demands of dosing session (i.e. attend centre and remain in research facility for an extended period of time)
Unable to access virtual meetings/phone for remote follow-ups
Limited life expectancy (<18 months)
Patients consuming more than 35 units of alcohol per week

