### Analysis strategy

Our two primary, mechanistic hypotheses relate to EEG and MRI:

H1 (EEG): We hypothesise an increase in signal complexity (LZc) at peak drug effects under psilocybin.H2 (fMRI): we hypothesise a decrease in brain network modularity after PAT.

Secondary outcomes include:

Reduced alpha power under psilocybin.A relationship between acute increases in LZc and post-PAT changes in psychological flexibility, measured by the BEAQ.Changes in mass univariate functional connectivity after PAT.Changes in PFC-tract diffusivity after PAT.Changes in EEG ERP related markers of functional plasticity after PAT.Changes in pain symptomatology after PAT, measured by the BPI-IS.

All secondary outcomes will be exploratory (see **Table 5**). Sub-acute EEG analyses will follow previously outlined protocols (91–93). With an assumption of high co-linearity between core outcomes we would explore data reduction approaches (e.g., factor or principal component analyses or canonical correlation analysis) to investigate key contrasts. Two tailed tests will be performed if findings are not aligned with prior hypotheses. Due to prior hypotheses (above) on directionality, one tailed t-tests will be appropriate to perform for H1 & H2. Multiple comparisons corrections and Bayesian analyses will be performed where deemed appropriate. Please see **Table 5** for timepoints for each analysis.

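### The number of tails for H1 and H2 depends on the observed result, so each test rejects at 1.5 times its nominal level, with all of the excess in the direction opposite to the hypothesis

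*Protocol article*

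**What the plan says.** The Analysis strategy section of the protocol article gives each of the two primary hypotheses a direction. For EEG, H1 reads: "We hypothesise an increase in signal complexity (LZc) at peak drug effects under psilocybin". For fMRI, H2 reads: "we hypothesise a decrease in brain network modularity after PAT". Because these directions were set beforehand, the section says that "one tailed t-tests will be appropriate to perform for H1 & H2". The sentence just before that one sets a different condition: "Two tailed tests will be performed if findings are not aligned with prior hypotheses".

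On multiplicity, the same section says only: "Multiple comparisons corrections and Bayesian analyses will be performed where deemed appropriate". The article gives no significance level anywhere, and nothing in it lowers the level to allow for a change in the number of tails. The design is a "single arm, fixed sequence, single-blind, within-subjects study", and the Recruitment section sets the size: "We will recruit up to twenty participants with fibromyalgia".

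**The concern.** A one-tailed test holds its level because the analyst gives up, in advance, any claim of significance in the other direction. The plan does not give it up. It keeps the whole of alpha for the predicted tail and, when the result does not fit the prediction, also allows a two-tailed test, which brings in a further alpha/2 on the far side. The procedure as a whole can then declare significance in both directions, and its total rejection rate exceeds the level that any one reported test would claim.

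What is at stake is how a surprising result is reported. If LZc fell under psilocybin, or modularity rose after therapy, the plan would allow that to be presented as significant by an ordinary two-tailed test, although the predicted tail had already used the full error allowance. The article is published before data collection to make the analysis accountable, and a choice of test made after seeing the result works against that purpose.

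**Working it through.** **Inputs.** From the Analysis strategy section: one-tailed tests for H1 and H2; two-tailed tests when findings do not fit the prior hypotheses; predicted directions up (H1) and down (H2). From Recruitment: at most 20 participants, so a paired t-test has up to 19 degrees of freedom. Alpha is not in the article; 0.05 is assumed here, with a range of 0.01 to 0.10. The article has no error-rate, power or sample-size figure to reproduce.

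**Step 1: size of the rule for one hypothesis.** Orient t so that positive values are in the predicted direction. Under no change,

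P(reject) = P(t > t[1 − alpha]) + P(t < −t[1 − alpha/2]) = alpha + alpha/2 = 1.5 × alpha.

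| alpha | predicted tail | opposite tail | total |
|---|---|---|---|
| 0.01 | 0.01 | 0.005 | 0.015 |
| 0.025 | 0.025 | 0.0125 | 0.0375 |
| 0.05 | 0.05 | 0.025 | 0.075 |
| 0.10 | 0.10 | 0.05 | 0.15 |

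Exact t tails give the same totals at n = 16 and n = 20. The factor of 1.5 depends neither on the sample size nor on the alpha chosen.

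**Step 2: does the meaning of the trigger matter?** A result could fail to fit the hypothesis because (A) its sign is opposite, or (B) the one-tailed test is not significant. Under B, a predicted-direction result that misses the one-tailed threshold also misses the stricter two-tailed one, so the only rejections added are again in the opposite tail. In 1,000,000 simulated null data sets with n = 20 and alpha 0.05, both readings gave 0.0748. Fixing the tails in advance gave 0.0499 (always one-tailed) and 0.0500 (always two-tailed).

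**Step 3: where the excess lies.** H1 predicts an increase and H2 a decrease. A false confirmation of either needs t > t[1 − alpha], which has probability alpha with or without the switch. The added alpha/2 consists wholly of opposite-direction claims.

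**Step 4: both hypotheses together.** If H1 and H2 were independent and uncorrected at 0.05:

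- without the switch, 1 − (1 − 0.05)² = 1 − 0.9025 = 9.75%;
- with the switch, 1 − (1 − 0.075)² = 1 − 0.8556 = 14.4%.

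**Step 5: power if two-sided testing is chosen instead.** These figures are for a paired t-test with n = 20 and alpha 0.05, from the noncentral t with 19 degrees of freedom and noncentrality dz × √20. The standardised effects dz are assumed; the article gives none.

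| assumed dz | noncentrality | one-sided 0.05 | two-sided 0.05 |
|---|---|---|---|
| 0.6 | 2.68 | 83% | 72% |
| 0.8 | 3.58 | 96% | 92% |

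These figures fit H1 best, since Table 5 compares two dosing days for LZc. For modularity it lists three timepoints, so a single paired t-test is a further assumption for H2.

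**The case against.** The best defence is that the authors may have meant something harmless: two-tailed tests for outcomes with no prior direction, one-tailed tests for H1 and H2. The wording does not say that. It conditions on findings rather than on outcomes, it is not limited to secondary outcomes, and the next sentence appeals to the same prior hypotheses for H1 and H2. Even if it were confined to secondary outcomes, choosing tails after the result would still need rewording.

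Several other objections stand, and they limit the point:

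- A reader might infer that the plan sets a 5% level which really runs at 7.5%. The article states no level, so only the factor of 1.5 holds without an assumption.
- A reader might infer that the chance of wrongly confirming H1 or H2 is inflated, or that all the primary p-values are wrong. Step 3 shows otherwise: a one-tailed p-value in the predicted direction remains valid.
- A reader might set the joint figure of 14.4% against 5%. The right comparator is 9.75%, because two uncorrected tests reach that without any switch. The gap between 5% and 9.75% is multiplicity, a separate matter.
- A reader might conclude that one-tailed testing is itself the fault. It is openly declared and is valid if fixed in advance; the fault is the switch.
- A reader might extend the point to the BEAQ, which the Abstract names as a primary outcome. The article limits one-tailed tests to H1 and H2 and does not say that the BEAQ is tested that way.

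Finally, this is a small, single-arm study with an early mechanistic aim, and the excess error falls only on results against the hypothesis. That bears on the severity; the defect remains.

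**Conclusion.** The concern holds in a limited form. As written, the sidedness of the primary tests follows the result, and the total false-positive rate under no change is 1.5 × alpha for each hypothesis. That factor assumes only that the test statistic is symmetric about zero under the null, as the t-statistic is. The step from 0.05 to 0.075 also assumes a 0.05 level, and the joint rise of 4.7 percentage points (14.4 − 9.75, rounded) further assumes independent, uncorrected tests. The excess is confined to claims opposite to the hypotheses.

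This is a rule that the article states and fixes badly, rather than a detail left to an unseen analysis plan. It should be corrected before results are seen, but in a study of this size and purpose it is not a fatal flaw.

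**What to change.** Delete the switching sentence, state alpha, and fix the sidedness of H1 and H2 before the data are seen, in one of two ways:

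- **(a)** Keep one-tailed tests at the stated alpha, and report any opposite-direction result descriptively, with no claim of significance. This brings the total rejection rate back to alpha and costs no power in the predicted direction.
- **(b)** If effects in both directions are of interest, test two-sided at the stated alpha whatever direction is observed. With the assumed effects in Step 5, this costs 11 percentage points of power at dz = 0.6 (83% to 72%) and 4 points at dz = 0.8 (96% to 92%).

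Either way the change is a sentence or two in the Analysis strategy section and does not touch data collection.

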## IMP management

A Schedule 1 licence for possession and storage of psilocybin has been obtained from the UK Home Office. Psilocybin supplied by Usona Insitute. Manufacture and encapsulation will be performed by Lonza Pharma and Biotech. Good Manufacturing Practise (GMP) will be maintained at all stages of manufacture. The IMP will be stored in a secure safe at Imperial College London, Hammersmith Campus.

## Data management

Data will be managed as per the Imperial College Data Management Standard Operating Procedures and a study- specific data management plan. All data collection and management softwares have been meet GDPR standards and have been approved by Imperial College London.

## Dissemination

The results of this study will be published in academic journals and presented in both the academic and public domain, including at scientific conferences and in the media in public engagement forums. Patient confidentiality will be maintained in all the above. All publications and presentations relating to the study will be overseen by the P.I and C.I. Authorship of parallel studies initiated outside of the Study Co-ordination Team will be according to the individuals involved in the project but must acknowledge the contribution of the Study Coordination Team.

## Ethics and trial registration

This study has received a favourable opinion from the London Central Research Ethics Committee and is sponsored by Imperial College London’s Research Governance and Integrity Team. All participants will provide their written informed consent to be screened and, if relevant, participate in this study. The Medicines and Healthcare products Regulatory Agency (MHRA) has confirmed its status as a non-clinical trial and waived the need for MHRA approval. The study has been reviewed and approved by the Health Research Authority (HRA). The study protocol has undergone external peer review and was co-developed with patient advisors. All staff have undergone Good Clinical Practice (GCP) training. The study has been adopted by the National Institute of Health Research (NIHR) Clinical Research Network (CRN) and has been registered on clinicaltrials.gov (NCT05548075). All study sessions will take place at the NIHR-funded Imperial College Research Facility (ICRF) and Imperial Clinical Imaging Facility (CIF).

## Conclusion

By publishing the study protocol, we aim to improve methodological transparency, rigour, and accountability and subsequently contribute towards more impactful outcomes. We also aim to highlight the importance of patient involvement in protocol design in generating relevant and equitable research. This study will investigate effect of psilocybin on the neural mechanisms in a fibromyalgia population. The results will provide the first EEG recordings of the acute psychedelic state in a clinical population. Further, they may inform the viability of psilocybin as a potential treatment option and help shape subsequent clinical trials.

## Data availability statement

The original contributions presented in the study are included in the article/supplementary material. Further inquiries can be directed to the corresponding author.
